### Intervention assessment

All subjects of the intervention group additionally receive intervention assessment immediately after baseline assessment. The current nutrition status is measured by the Mini Nutrition Assessment (MNA) [27]. Other health dimensions of elderly persons such as impaired sight or hearing, urinary or bowel incontinence and loss of functional muscle mass are assessed with the Geriatric Screening AGAST [28] and the Geriatric Screening by Lachs [29]. These geriatric screenings also determine social activities, housing conditions, economical conditions and polypharmacy. The Clock-Completion Test [30] will complement the MMSE for the baseline assessment of cognitive abilities.

### Case conferences

We will conduct interdisciplinary case conferences for all patients in the intervention group. We intend to collect several cases for a conference. We will conduct case conferences in the defined period of 3 weeks between first and second home visit in this way trying to standardize the procedures. Cases will be prepared and introduced to the conference group by the visiting investigator. The investigators will invite appropriate health professionals as the case requires. The professional spectrum of the conference expert advisory group hereby consists of nurses, a general practitioner, a nutritionist, a geronto psychiatrist, a physiotherapist, a psychologist and a social worker. Recommendations will be worked out for the single patient and we will document them for the next home visit. The duration of the preparation, present experts and duration of the conference will be documented for each patient individually.

### Home counseling intervention

The last part of the experimental intervention consists of a counseling intervention. We will address the identified problems and present the recommendations of our expert advisory group during this home visit. We estimate the duration of the second home visit including the counseling with 20–40 minutes.

### Booster session

Four weeks after the counseling home visit we will visit the patients in the intervention group for a third time. During this visit we want to evaluate which recommendations the patients already implemented and which not. In this way we can assess obstacles and facilitators to the recommendation adherence. Additionally, we have the opportunity to boost our recommendations from the second home visit.

### Follow-up

18 months after the first home visit we will assess all participants using the same measurement as for the baseline assessment. Additionally, details about current residence status, nursing home admission and date of nursing home admission are included. If a subject cannot be reached by usual means like telephone or mail, the named contact person or residents' registration office will be contacted.

All measurements are summarized in Table 1.

**Table 1 T1:** Measurements

Points of measurement and outcome measures according to case report form	
**point of measurement**	**outcome measures**

Screening	▪ sociodemographic data
	▪ ADL – Activities of Daily Living [13]
	▪ document analysis

Baseline assessment	▪ EQ-5D [12]
	▪ Chronic Disease Score [26]
	▪ Number of falls during the last 12 months
	▪ Questionnaire of Service Utilization and Costs [20-25]
	▪ Barthel-Index [18]
	▪ MMSE – Mini Mental State Examination [14]
	▪ SoS – Social Situation [15]
	▪ 5-item version of the Geriatric Depression Scale [16]
	▪ IADL – Instrumental Activities of Daily Living [19]

Intervention assessment	▪ MNA – Mini Nutrition Assessment [27]
	▪ Clock-Completion Test [30]
	▪ Geriatric Screening AGAST [28]
	▪ Geriatric Screening by Lachs [29]

Follow-up	▪ same as Baseline

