### Blinding

Patients and field researchers cannot be blinded to group allocation. A blinded statistician not involved in trial conduct will do the final analysis.

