### Outcomes

Primary outcome of our trial is the incidence of nursing home admission over the study period of 18 months. Nursing home admission in our trial is defined as the permanent admission into an inpatient nursing care facility according to the social security code of Germany. Short term care, assisted living, geriatric day care or respite care facilities are not included in this definition.

Data will be collected on follow-up assessment either by direct contact with the participants, their relatives or the resident registration office.

Secondary outcomes over the whole trial period of 18 months:

• Time to nursing home admission

• health care service utilization and costs

• incremental cost-effectiveness and cost-utility ratio

• health related functioning

• health related quality of life

• prevalence of falls

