### Drop-outs

Drop-outs will be documented thoroughly and included in data analysis to the point of drop-out. Reasons for drop-out will be reported and analyzed.

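### Reachable participants who stop taking part can be left without an 18-month nursing home status, because the registration office or contact person is consulted only for people who cannot be reached

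*Protocol article*

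**What the plan says.** All references are to the protocol article.

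- **Outcomes.** "Primary outcome of our trial is the incidence of nursing home admission over the study period of 18 months". The definition is narrow: "Nursing home admission in our trial is defined as the permanent admission into an inpatient nursing care facility". Short stays, day and respite care and assisted living do not count. The information comes "either by direct contact with the participants, their relatives or the resident registration office".
- **Follow-up.** Participants are assessed directly 18 months after the first home visit. The other sources have one trigger: "If a subject cannot be reached by usual means like telephone or mail, the named contact person" or the registration office is approached.
- **Drop-outs.** They are "included in data analysis to the point of drop-out".
- **Data analysis.** All outcomes are compared between the arms by intention to treat.
- **Blinding.** "Patients and field researchers cannot be blinded to group allocation". The statistician is blinded.
- **Sample size calculation.** 20% versus 7%, two-sided 5% test, 80% power and 30% drop-out give 160 per arm.

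**The concern.** The Outcomes section lists three sources without saying that any one of them is used for everybody. The Follow-up section says when a source other than direct contact is used, and its trigger is being unreachable. A person who answers the telephone and says no is reachable, so the trigger is not met. The Drop-outs section then uses that person's data only up to the refusal.

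For a yes/no outcome counted over 18 months, data up to an earlier point leave the status unknown. Two things follow.

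1. **Loss related to the outcome.** People who have moved, are about to move or are declining are plausibly the ones who stop. If such loss is unequal between arms, the comparison of admission rates is biased.
2. **Lost precision.** The plan budgets for 30% loss on an outcome for which it already names a record source.

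A lesser worry is that reports are collected by staff who know the allocation, while the endpoint needs a distinction between a permanent admission and a temporary stay.

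**Working it through.** **Step 1. Which route applies to whom, as written**

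| Participant at 18 months | Route stated | Status known? |
|---|---|---|
| Reached and willing | Direct assessment | Yes, from the report |
| Cannot be reached | Contact person or registration office | Probably |
| Reached, declines to go on | None triggered; data used up to drop-out | Not assured |

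The third row is the gap. The Outcomes list would permit a lookup for these people, but no sentence calls for one.

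**Step 2. The plan's own sample size**

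Inputs from Sample size calculation: p1 = 0.20, p2 = 0.07, difference d = 0.13, two-sided alpha 0.05, power 0.80, drop-out 30%. Mean p = 0.135.

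- n = [1.96·√(2·0.135·0.865) + 0.842·√(0.20·0.80 + 0.07·0.93)]² / 0.13² = 108 per arm after rounding up.
- With continuity correction, 123 per arm. 123 × 1.3 = 159.9, so 160, the stated figure.
- Without correction, 108 / 0.7 = 154.3, so 155 per arm.

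The stated 160 is therefore reproduced with the continuity correction and multiplication by 1.3.

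**Step 3. Power by number with known status** (uncorrected two-sided test)

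Power = Φ{[d − 1.96·√(2·0.135·0.865/n)] / √(0.2251/n)}, where 0.2251 = 0.20·0.80 + 0.07·0.93.

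| Status unknown | n per arm | Power |
|---|---|---|
| 30% | 160 × 0.7 = 112 | 81.7% |
| 20% | 128 | 86.5% |
| 10% | 144 | 90.2% |
| 0% | 160 | 92.9% |

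For n = 112: (0.13 − 1.96 × 0.0457) / 0.0448 = 0.90, and Φ(0.90) is about 0.817.

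**Step 4. Illustration of outcome-related loss** (the loss patterns are assumptions; the documents give none)

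True rate 20% in both arms and 30% lost in each. In the control arm loss is unrelated to admission. In the intervention arm a share a of admitted and a share b of non-admitted people are lost, with 0.2a + 0.8b = 0.30. Observed rate = 0.2(1 − a) / 0.70.

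| a | b | Observed rate, intervention | False rejection of the nominal 5% test, 112 per arm |
|---|---|---|---|
| 30% | 30% | 20.0% | 5.0% |
| 40% | 27.5% | 0.12/0.70 = 17.1% | 8.5% |
| 50% | 25% | 0.10/0.70 = 14.3% | 20.5% |
| 60% | 22.5% | 0.08/0.70 = 11.4% | 42.1% |

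**Step 5. Illustration of under-capture in one arm** (also assumed; 112 per arm)

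If 90%, 80% or 70% of admissions are captured in one arm and all in the other, a true 20% in both arms gives false rejection of 6.7%, 12.2% or 22.2%. With a true 20% versus 7% and under-capture in controls only, power falls from 81.7% to 70.4%, 56.1% or 40.0%.

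**The case against.** The retrieval rule is the same in both arms, and the Follow-up section says that all participants are assessed. Relatives count as a source, so the outcome does not rest on self-report alone. The definition is tied to the social security code and leaves limited room for judgement. The extra contact in the intervention arm also ends early: three weeks between the first and second visit plus four weeks to the booster is about 7 weeks. Roughly 71 of 78 weeks then pass without scheduled contact in either arm. The term drop-out is not defined, and using data up to that point is a natural rule for the secondary outcome, time to admission. Finally, an address record may not separate a permanent admission from assisted living or a short stay.

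Most of this stands, and it rules out several stronger readings that a reader might infer:

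- **That sources or completeness do differ by arm.** With one rule for both arms, this is a risk; no section shows it.
- **That everyone who refuses visits is excluded from the primary analysis.** The article does not say so. It only fails to provide a route to their status.
- **That unblinded staff classify admissions.** Field researchers are unblinded, but no section says who decides whether an admission is permanent.
- **That most of the 30% loss is avoidable.** Its make-up is not stated. In impaired people over 80, part of it may be death, which no query undoes.

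The objection does not remove the gap in Step 1. The only stated trigger misses reachable people who stop, and the Drop-outs rule does not bring them back. The analysis plan is not shown and may deal with missing status statistically, but that is weaker than obtaining a status that a named source may hold.

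**Conclusion.** The point holds in a limited form and is worth acting on. Read together, Follow-up and Drop-outs can leave reachable people who decline further participation without an 18-month status. That conflicts with the intention-to-treat comparison promised in Data analysis and opens the way to outcome-related loss, with unblinded field staff collecting the reports.

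On precision, power is 81.7% if 30% are lost and at most 92.9% if nobody is. The second figure is an upper bound, because deaths and objections will remain. Both rest on the planned 20% versus 7% and an uncorrected two-sided test.

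On bias, the size is unknown. The illustrations show that modest imbalance does little (10% of admissions missed in one arm raises false rejection from 5% to 6.7%), while strongly outcome-related loss in one arm could do much more (20.5% if half of the admitted people there are lost). The documents give no evidence for any particular pattern or direction.

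**What to change.** 1. In Drop-outs and Follow-up, state that ending visits or assessments does not end follow-up for the primary outcome.
2. At 18 months, unless the person objects, obtain residence, date of move and date of death from the registration office for every randomised participant in both arms.
3. For any move to a facility, confirm with the contact person or the facility whether it is a permanent admission under the definition in Outcomes. The address alone should not decide this.
4. Where existing staff allow, have this coded with the arm label removed.

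**Cost.** Up to 320 queries with their fees, a line in the consent form, some confirmation calls, and data-protection handling that keeps identifying address data apart from the pseudonymised trial data, as Protection of data privacy requires. No extra visit is needed. The trial already cooperates with a registration office for recruitment and already names it as an outcome source. Ethical considerations provides for changes by amendment to the ethics committees.

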### Study procedure

A liaison nurses screens and recruits the participants for eligibility in the 2 hospitals in Halle. Medical secretaries screen and recruit the participants in Leipzig and Halle for eligibility in the participating GPs' practices. Patients then are randomized by the local study center via consecutive randomization lists in this way assuring concealed allocation of participants. The participants are contacted by the centers' study personal via mail and phone. In the phone call an appointment for the first home visit is made with the patients. In Halle we additionally will contact the patients after discharge from hospital. All other study procedures are standardized across the study centers, in this way ensuring a homogenous conduct of the trial.

The intervention group will be assessed with a geriatric assessment and the baseline assessment. A team of nurses, psychologists, physiotherapists, dietitians and physicians will work out individualized recommendations in a case review one week after the geriatric assessment. The main aim is to identify self-care deficits and risks for self-care deficits in the socioeconomic supportive dimension, the social integrative dimension and finally the health dimension. Then appropriate recommendations will be given by the team. After the case conference the members of the intervention group are visited by the same staff member again. This staff member will conduct a consultation and instruction based on the results of the case conference. Four weeks after the consultation another visit is done by the staff member. This visit (booster session) is for evaluative purposes mainly: To what extent the study participant adheres to the recommendations and how convenient are the recommendations. The final measurement will be the follow-up assessment 18 months after baseline.

The control group is only assessed with the baseline assessment and the follow-up assessment 18 months later. The control group will not receive any intervention in addition to standard care. The flow of the participants is shown in Figure 1.

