### Baseline assessment

All participants (intervention and control group) receive baseline assessment after randomization and the same assessment at follow-up after 18 months. Cognitive function is assessed using the Mini Mental State Examination (MMSE) [14]. The health related quality of life is measured by the EuroQol-5D [12], including a visual analogue scale (VAS) to measure patients preferences. Psychosocial factors are assessed with the Social Situation by Nikolaus (SoS) [15]and the 5-item version of the Geriatric Depression Scale (GDS)[16]. This short form was chosen because it is as effective as the 15-item version of the GDS [17], which is widely used for depression screening in cognitively unimpaired elderly persons. Moreover, the 5-item GDS is more an economical version because of reduced administration time. Details about the functional status will be determined using the Barthel-Index [18] and the Instrumental Activities of Daily Living (IADL) [19]. Additionally, all participants are asked about their history of falls in the past 12 months. A Questionnaire of Service Utilization and Costs will be used based on cost diaries used in earlier studies [20-25].

This questionnaire also includes sociodemographic data (i.e. age, sex, marital and educational status, life conditions); information about health insurance, long term care insurance and the degree of impairment to receive benefits from the long term care insurance. Furthermore the Chronic Disease Score will be calculated [26].

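### Falls are an 18-month outcome, but the follow-up question covers only the last 12 months, so the first six months, which contain all three home visits, are not measured

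*Protocol article*

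**What the plan says.** **Outcome.** The Outcomes section puts "prevalence of falls" in a list headed "Secondary outcomes over the whole trial period of 18 months".

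**Instrument.** The Baseline assessment section says that "all participants are asked about their history of falls in the past 12 months". Table 1, in the Follow-up section, lists the item as "Number of falls during the last 12 months".

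**Use at month 18.** Three statements carry the item forward unchanged:
- The Baseline assessment section says participants receive "the same assessment at follow-up after 18 months".
- The Follow-up section says "18 months after the first home visit we will assess all participants using the same measurement as for the baseline assessment".
- The follow-up row of Table 1 reads "same as Baseline".

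The Follow-up section names three additions for month 18: where the participant now lives, whether a nursing home admission has occurred, and its date. Falls are not among them.

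**Interim contact.** The Study procedure section states: "The control group is only assessed with the baseline assessment and the follow-up assessment 18 months later".

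**The concern.** The article fixes both the period of the outcome and the recall window of the only question that measures it, and the two differ by six months. Falls in that half-year are never asked about, so no later analysis can recover them.

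Two things are at stake. First, the result available at the end is a 12-month figure for months 6 to 18. If it is presented under the present outcome heading, it will be read as an 18-month prevalence and will understate it. Second, the missing months are the first after baseline, when the assessment, the counselling and the booster visit are delivered. An effect on falls that appears early and then fades would not be seen.

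**Working it through.** The article gives no falls rate and no power calculation for falls, so there is no stated figure to reproduce. The main check is date arithmetic.

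**1. Windows covered** (month 0 = first home visit)

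| Source | Asked at | Period covered |
|---|---|---|
| Outcomes section, period required | – | 0 to 18 |
| Baseline falls item, 12-month recall | month 0 | −12 to 0 |
| Follow-up falls item, 12-month recall | month 18 | 18 − 12 = 6, so 6 to 18 |

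Uncovered: months 0 to 6, which is 6/18 = 33% of the outcome period.

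**2. Other possible sources of falls data**
- The control group has no assessment between baseline and month 18 (Study procedure).
- The booster visit is for the intervention group only, and it is described as checking uptake of the recommendations (Study procedure; Booster session).
- The service utilization and cost questionnaire is not described as counting falls, and its recall period is not given.
- No falls diary or calendar is described.

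None of these supplies months 0 to 6 in both arms.

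**3. Where the visits fall**
- Visit 1 is at month 0.
- Visit 2 is about 3 weeks later (Case conferences).
- Visit 3 is 4 weeks after visit 2 (Booster session), so at week 3 + 4 = 7, or 7/4.345 = 1.6 months.
- The Study procedure section places the case review one week after the geriatric assessment. If visit 2 followed straight after it, visit 3 would be at week 1 + 4 = 5, or 5/4.345 = 1.2 months.

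On either reading all three visits lie in the uncovered period.

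**4. How far a 12-month figure would understate an 18-month one**

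The 12-month prevalences p of 30%, 40% and 50% are assumptions, chosen to show a range.

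*Same constant fall rate in everyone:* 18-month prevalence = 1 − (1 − p)^1.5.

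*Fall rates that differ between people* (gamma-distributed with shape 1, also an assumption): with θ = p/(1 − p), 18-month prevalence = 1.5θ/(1 + 1.5θ).

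| Assumed 12-month p | 18-month, same rate | Gap | 18-month, varying rates | Gap |
|---|---|---|---|---|
| 30% | 1 − 0.70^1.5 = 41% | 11 points | 0.643/1.643 = 39% | 9 points |
| 40% | 1 − 0.60^1.5 = 54% | 14 points | 1.000/2.000 = 50% | 10 points |
| 50% | 1 − 0.50^1.5 = 65% | 15 points | 1.500/2.500 = 60% | 10 points |

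These gaps concern the level of the prevalence, not the difference between the arms.

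**The case against.** The strongest reply is that the outcome heading is loose. It also covers quality of life and functioning, which are measured at single time points and cannot run over 18 months. Falls are called a prevalence, whereas the primary outcome is called an incidence. A 12-month period prevalence taken at the final visit and matched to the baseline item is a defensible choice, and the fault would then be only an imprecise heading. This is a possible reading, but the article does not state it. The heading as written says 18 months, and one of the two passages has to change.

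The second reply is that the comparison survives. Both arms get the same question at the same time, so the window alone does not bias a comparison over months 6 to 18. That stands. It is also true that a sustained effect would still be visible: from the booster at about month 1.6 to month 18 is 16.4 months, and the item covers 12 of them, 12/16.4 = 73%. What is lost is an effect confined to the first six months. The weeks of delivery are not necessarily when an effect on falls would be largest, since participants are still taking up the recommendations at the booster.

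Third, the understatement in percentage points rests on assumed prevalences and is smaller if fall rates differ between people. That is correct. The 11 to 15 points belong to the equal-rate assumption and mark the upper end of the illustrations; allowing for variation gave 9 to 10.

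Finally, the full case report form is not shown and might word the follow-up item differently. Table 1, however, presents itself as following that form, and its follow-up row gives no change.

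**Conclusion.** The concern holds. As described, the data cover months 6 to 18 only, so the stated 18-month falls outcome cannot be obtained. The loss of 6 of 18 months (33%) follows from the article's own dates, and all three home visits lie within it. This rests on the follow-up item being worded as at baseline, which the article says three times.

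The size in prevalence terms is illustrative. A 12-month figure would be about 9 to 15 percentage points below the 18-month prevalence, for assumed 12-month prevalences of 30% to 50% and depending on how much fall rates vary between people.

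The weight is moderate. Falls are one of six secondary outcomes, the comparison over months 6 to 18 is not biased by the gap itself, and the primary outcome and the sample size of 320 are untouched. It should be corrected because an unasked period cannot be recovered at analysis.

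**What to change.** Choose one of two changes.

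1. **Keep the 18-month outcome.** At follow-up, ask about falls since the first home visit, anchored to its date, and keep the 12-month item for comparison with baseline. State which answer defines the secondary outcome. The cost is one added question. The drawback is that recall over 18 months is less reliable than over 12, particularly at this age.
2. **Keep the 12-month item alone.** Redefine the outcome in the Outcomes section as falls in the 12 months before the month-18 follow-up, and say that the first six months are not observed. The cost is a wording change. The drawback is that any effect confined to those months stays unmeasured.

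In either case, say how the prevalence is derived from the recorded number of falls, for example as the proportion with at least one. The baseline 12-month falls history is already collected and can serve as a covariate in the planned regression. The amendment route in the Ethical considerations section covers either change.
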